#### Secondary End Points

The secondary study end points include perioperative safety, postoperative nutritional status, and postoperative quality of life.

Perioperative safety primarily encompasses the duration of surgery, amount of intraoperative blood loss, and postoperative complication status. Nutritional status and quality of life following surgery will be assessed at the 3rd, 6th, and 12th postoperative months. Postoperative nutritional status will be determined based on changes in patient weight, hemoglobin levels, total protein levels, albumin levels, total lymphocyte count, and PNI. Additionally, patients’ quality of life will be evaluated via the EORTC QLQ-C30 and daily food intake frequency. The Visick score will be used for assessing patients’ symptoms and quality of life [21]:

Grade I—patients are asymptomatic or have only mild symptoms that do not significantly affect their quality of life. Surgical outcomes are considered excellent.Grade II—patients experience mild symptoms that have minimal impact on their daily activities. Overall, patients are satisfied with the surgical outcome.Grade III—patients have moderate to severe symptoms that affect their daily lives. These symptoms may require medical treatment or lifestyle modifications. The surgical outcome is considered less favorable.Grade IV—patients have severe symptoms that significantly impact their quality of life. The surgical procedure has failed to achieve the desired outcome. Further surgical intervention or other treatments may be necessary.

### Power and Sample Size

This study is designed as a prospective randomized controlled trial with a noninferiority objective. It comprises 2 groups: the experimental group (tunnel anastomosis group) and the control group (double-tract jejunal interposition reconstruction group).

The reported incidence of reflux esophagitis for DTJIR in the literature varies widely, ranging from 1.7% to 25%. However, most contemporary studies report rates concentrated at approximately 10% [22-24]. On the basis of retrospective data from our center, the incidence of reflux esophagitis for TA is approximately 5%. Therefore, the estimated incidence of reflux esophagitis was 10% in the DTJIR group and 5% in the TA group. With a significance level set at α=.025 (one sided), a power of 1 – β of 0.80, a noninferiority margin of 0.05 (given the reported incidence of reflux esophagitis with the current surgical options, a noninferiority margin of ≤5% was deemed clinically acceptable as such a difference would not offset the significant benefits associated with the new technique), a 1:1 ratio between the experimental and control groups, and an anticipated dropout rate of 10%, the sample size was calculated via the PASS software (NCSS, LLC). The resulting sample sizes for both groups were 120 patients each.

Therefore, a total of 240 patients will be included in this study, with 120 patients in the experimental group and 120 patients in the control group.

### Data Collection

Basic patient information and clinical data will be collected before discharge, including identity card number; gender; age; contact information; date of operation; surgical approach; duration of surgery; intraoperative blood loss; pathological tumor, node, metastasis staging; number of lymph nodes dissected; number of positive lymph nodes; length of postoperative hospital stay; and postoperative complications. Each patient will be followed up on at the 3rd, 6th, and 12th months postoperatively, and the following data will be collected regarding their postoperative quality of life: daily meal frequency, Visick score, and postoperative quality of life score (using the EORTC QLQ-C30), as well as data on their postoperative nutritional status, including weight change, hemoglobin level, total protein level, albumin level, total lymphocyte count, and PNI.

The basic information and clinical data for each patient collected before discharge will be classified, stored, and entered into the database. The results of each follow-up will be meticulously recorded and entered into the database alongside the other data. All electronic data will be backed up to prevent loss.

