## Introduction

Gastric cancer is a type of cancer with high morbidity and mortality in China, and the incidence of proximal gastric cancer is currently increasing [1-3]. Surgical treatment for proximal gastric cancer involves either total gastrectomy or proximal gastrectomy. Research has shown that proximal gastrectomy has the same therapeutic potential and efficacy as total gastrectomy, with advantages in terms of postoperative weight loss, dumping syndrome, anemia, and nutritional supplementation [4-10]. However, the issue of reflux esophagitis following proximal gastrectomy remains a significant challenge for surgeons [11]. Numerous studies have been conducted on antireflux techniques for digestive reconstruction, including double-tract jejunal interposition reconstruction and the double-flap technique (Kamikawa anastomosis), which have exhibited promising antireflux effects. Nevertheless, there is still no consensus on which reconstruction method should be considered the standard [12-17].

Tunnel anastomosis is a novel technique for digestive tract reconstruction following proximal gastrectomy. Owing to its preservation of an intact muscular flap, it ensures superior blood supply to the anastomotic site. A previous study by our team demonstrated that the antireflux effects of this technique are favorable [18]. Double-tract jejunal interposition reconstruction is currently the mainstream method for digestive tract reconstruction following proximal gastrectomy and is widely recognized by most experts [19]. The incidence of postoperative reflux esophagitis following this procedure is approximately 10%. Therefore, we selected this technique as the control group to further validate the effectiveness of TA.

We hypothesize that tunnel anastomosis is noninferior to double-tract jejunal interposition reconstruction in preventing postoperative reflux esophagitis. The objective of this study is to further validate the surgical safety and antireflux effect of tunnel anastomosis and assess the efficacy and ability of this technique to improve the quality of life of patients following proximal gastrectomy. It is hoped that this research will contribute to enhancing the theoretical and clinical practice foundations for refining surgical treatment strategies for upper gastric cancer.

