### Follow-Up

Follow-up will be conducted by dedicated follow-up staff. All patients will undergo follow-up visits at 3 months, 6 months, and 1 year postoperatively. At these visits, hematological examinations and postoperative quality of life assessments (using the European Organisation for Research and Treatment of Cancer Quality of Life Questionnaire Core 30 [EORTC QLQ-C30] and 36-Item Short Form Health Survey) will be performed. Nutritional status will be assessed based on hematological test results, changes in body weight, and the prognostic nutritional index (PNI). In addition, reflux symptoms will be assessed via the Visick score. At the 1-year follow-up, gastroscopy will be performed to assess reflux esophagitis according to the Los Angeles (LA) classification.

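### The only stated collection time for postoperative complications is before discharge, so the safety window varies by patient and late anastomotic complications have no stated collection point

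*Protocol article*

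**What the plan says.** Surgical safety is part of the stated purpose. The Introduction says: "The objective of this study is to further validate the surgical safety and antireflux effect of tunnel anastomosis". Secondary End Points defines the safety component: "Perioperative safety primarily encompasses the duration of surgery, amount of intraoperative blood loss, and postoperative complication status". That section ties nutrition and quality of life to months 3, 6 and 12, but gives complication status no time window.

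The only time attached to complications is in Data Collection, where the first list opens "Basic patient information and clinical data will be collected before discharge, including identity card number; gender; age; contact information; date of operation; surgical approach" and closes "length of postoperative hospital stay; and postoperative complications". For months 3, 6 and 12 the same section turns to other items: "the following data will be collected regarding their postoperative quality of life: daily meal frequency, Visick score, and postoperative quality of life score", followed by weight change, blood measures and the prognostic nutritional index.

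Follow-Up describes the same visits: "At these visits, hematological examinations and postoperative quality of life assessments", together with nutritional status and the Visick score. It adds one procedure: "At the 1-year follow-up, gastroscopy will be performed to assess reflux esophagitis according to the Los Angeles (LA) classification". Neither section lists a complication item at a visit, and stenosis is not named anywhere in the article.

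The limitations paragraph of the Discussion states that patients, surgeons, radiologists and clinical assessors cannot be blinded.

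**The concern.** Two things follow if the collection schedule is applied as written.

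First, the period at risk for a recorded complication is the hospital stay. It differs from patient to patient and ends at an event that occurs after randomization. If stay differs by arm, the arms are observed for different lengths of time, and the arm discharged earlier records fewer complications even when the true rates are equal. In an unblinded trial, a difference in stay that partly reflects knowledge of the arm cannot be excluded.

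Second, complications that appear or are treated after discharge have no stated place in the data. The two reconstructions differ in structure: one esophagogastric anastomosis through a seromuscular tunnel against three anastomoses involving the jejunum. Late problems could therefore differ in either direction. Power and Sample Size justifies the margin partly by the benefits of the new technique, so an incomplete record of harm would weaken the trial's own argument when the result is interpreted.

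**Working it through.** **1. Collection times set side by side**

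| Section | Time stated | Complications listed? |
|---|---|---|
| Data Collection, first list | before discharge | yes, last item |
| Data Collection, second list | months 3, 6, 12 | no |
| Follow-Up | months 3, 6, 12; gastroscopy at 1 year | no |
| Secondary End Points | none for complications; months 3, 6, 12 for nutrition and quality of life | named as end point, no window |

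The only stated time for complications is therefore before discharge. The second list in Data Collection is not exhaustive: it omits the 1-year gastroscopy and the SF-36. Follow-Up schedules both of those, however. No section schedules complications after discharge.

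**2. The plan's own figure**

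The article computes nothing for complications. Its one design calculation supplies the arm size used below, and it reproduces. Inputs are 10% and 5% reflux esophagitis, margin 0.05, one-sided alpha 0.025, power 0.80 and dropout 10%:

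n = (1.960 + 0.842)² × (0.10×0.90 + 0.05×0.95) / (0.05 + 0.05)² = 7.849 × 0.1375 / 0.01 = 107.9, so 108; 108 / 0.90 = 120 per arm.

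**3. Effect of unequal windows (all inputs assumed)**

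Assume a true complication rate of 20% in both arms, exponential time to onset with mean m days, and observation ending at a fixed stay of s days.

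Recorded rate = 20% × (1 − exp(−s/m))

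| m (days) | 8 days | 10 days | Difference | 7 days | 12 days | Difference |
|---|---|---|---|---|---|---|
| 5 | 16.0% | 17.3% | 1.3 | 15.1% | 18.2% | 3.1 |
| 7 | 13.6% | 15.2% | 1.6 | 12.6% | 16.4% | 3.8 |
| 10 | 11.0% | 12.6% | 1.6 | 10.1% | 14.0% | 3.9 |

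The true difference is zero in every row. The apparent difference, in percentage points, always favours the shorter stay. The model is simple: it treats stay as unrelated to complications, whereas a complication may itself prolong the stay. The table therefore illustrates direction and order of size and is not a forecast.

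**4. Sampling error for comparison**

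At 20% in both arms with 120 patients each, the standard error of the difference is √(2 × 0.20 × 0.80 / 120) = 0.0516, or 5.2 points. The spurious differences above are smaller than one standard error.

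**5. Events outside the window (assumed rates)**

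If 1%, 3%, 5% or 10% of an arm had a complication arising after discharge, then 120 × rate = 1.2, 3.6, 6 or 12 patients per arm would fall outside the stated collection period.

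**The case against.** The strongest reply is that this is a condensed article and that silence is not exclusion. The month 3, 6 and 12 list leaves out even the gastroscopy that measures the primary end point, so absence from that list cannot prove that an item is not collected. Secondary End Points does not confine complication status to the hospital stay, and the end point is labelled perioperative safety, which fits collection around the admission. This stands against a reading that a reader might take from the schedule, namely that complications are never recorded after discharge. The documents do not say so. It does not remove the point, because the article does state a time for complications, and that time is before discharge.

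A reader might also infer that a stenosis would go wholly unrecorded. That is not supported. Meal frequency, weight, the QLQ-C30 and Visick grades III and IV could reflect it, and the 1-year gastroscopy could show it. But none of these is named as a complication measure, the Visick score does not identify a cause, and a stenosis treated before month 12 could be missed.

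Three further inferences lack support. The article does not say who decides discharge or by what criteria. It does not describe the tunnel as tight; it gives a flap of about 3 × 3.5 cm and an anastomotic caliber of 3 cm. It contains nothing to show that a narrowed anastomosis would count as a success on the primary end point.

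Finally, no passage indicates that stay will differ by arm, and length of stay is collected, so an imbalance would be visible. That is fair. Seeing an imbalance would not, however, recover the complications that arose after discharge.

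**Conclusion.** The point holds in a limited form and should be fixed. The plan states one collection time for complications, before discharge, and gives no fixed window. The window as written therefore varies by patient, ends at an event after randomization that may differ by arm in an unblinded trial, and leaves late anastomotic complications without a stated collection point, although surgical safety is an objective.

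The size cannot be derived from the documents, which give neither complication rates nor stays. The illustrative bias of 1.3 to 3.9 points rests wholly on the assumed 20% rate, the exponential onset and the chosen stays. The direction needs less: it holds whenever stays differ between the arms and some complications arise after discharge.

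The point concerns one component of a secondary end point. The primary end point, its analysis and the sample size are unaffected, so it does not call the trial's main conclusion into question.

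**What to change.** In Secondary End Points and Data Collection, define complication status over one fixed period from surgery, the same in both arms and regardless of discharge. Ninety days is one example, as it matches the 3-month visit. Then:

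- add fields to the existing 3-, 6- and 12-month forms for complications, readmission, reoperation and anastomotic stenosis since the last visit;
- record anastomotic patency at the 1-year gastroscopy already planned;
- report stenosis by arm beside the primary result.

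If the full protocol already sets such a window, the article's Data Collection text needs only to be brought into line with it.

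The cost is a few form fields and, for patients already enrolled, retrieval from records. No new visit or procedure is needed. Recruitment is planned to February 2027 and follow-up to February 2028, so later patients can be covered prospectively. The recorded complication rate will rise in both arms, and the report should explain why.

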### Statistical Analysis

Data analysis will be conducted by professional statisticians. In addition to the overall comparative analysis conducted between the TA and DTJIR groups, we will further perform subgroup analyses stratified by disease stage and surgical approach.

Intention-to-treat and per-protocol approaches will be applied for efficacy analysis. An as-treated approach will be used for safety analysis. For continuous variables, a normality test will be performed first. For those that conform to a normal distribution, the 2-tailed *t* test will be used for statistical analysis (all continuous values will be expressed as means and SDs). Those not conforming to a normal distribution will be presented as quartiles and rank means, and the Mann-Whitney *U* test will be used to calculate the *P* value to compare differences between groups. For categorical variables, the chi-square test will be used for statistical analysis. Repeated-measure data will be analyzed using a mixed-effects model. Subgroup analyses will be conducted by disease stage (early vs advanced); surgical approach (open, laparoscopic, or robot-assisted); age; macroscopic types; and tumor, node, metastasis stage. All *P* values calculated in the analysis will be 2-sided, and *P*<.05 will be considered statistically significant. If missing data constitute more than 5%, multiple imputations will be conducted. Statistical analyses will be performed via SPSS (IBM Corp), Prism (GraphPad Software), or PASS.

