### Assessment of Outcomes

#### Primary End Points

The primary end point is the incidence of reflux esophagitis, which will be determined via gastroscopy results 1 year postoperatively. To determine the severity of reflux esophagitis, the modified LA classification system for reflux esophagitis will be used, which is considered a reliable method for categorizing reflux esophagitis. The modified LA classification criteria are as follows [20]:

Grade N—normal mucosaGrade M—minimal changes to the mucosa, such as erythema and/or whitish turbidityGrade A—nonconfluent mucosal breaks of <5 mm in lengthGrade B—nonconfluent mucosal breaks of >5 mm in lengthGrade C—confluent mucosal breaks <75% circumferentialGrade D—confluent mucosal breaks >75% circumferential

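### The trial is sized for noninferiority with a 5-point margin, but the only test stated for its binary primary end point is a chi-square test of equality, so the margin is never used

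*Protocol article*

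**What the plan says.** The objective is stated consistently. The Introduction says "We hypothesize that tunnel anastomosis is noninferior to double-tract jejunal interposition reconstruction in preventing postoperative reflux esophagitis", and Power and Sample Size says "This study is designed as a prospective randomized controlled trial with a noninferiority objective". The primary outcome is binary: "The primary end point is the incidence of reflux esophagitis, which will be determined via gastroscopy results 1 year postoperatively".

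The design parameters, in Power and Sample Size, are "With a significance level set at α=.025 (one sided), a power of 1 – β of 0.80, a noninferiority margin of 0.05". The planning rates are given as "the estimated incidence of reflux esophagitis was 10% in the DTJIR group and 5% in the TA group". With 1:1 allocation and 10% dropout, the result is 120 patients per group.

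The Statistical Analysis section then assigns tests by type of variable. For categorical data: "For categorical variables, the chi-square test will be used for statistical analysis". It adds that all P values "values calculated in the analysis will be 2-sided", with significance at P<.05. Efficacy is to be analysed by intention to treat and per protocol. The section does not mention the margin, a confidence interval for the risk difference, or a rule for declaring noninferiority, and it does not exempt the primary end point from the general rule.

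**The concern.** The two sections test different null hypotheses. Write p_TA and p_DTJIR for the true 1-year rates of reflux esophagitis.

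- Design (Power and Sample Size): H0 is p_TA − p_DTJIR ≥ 0.05, and rejecting it establishes noninferiority.
- Stated test (Statistical Analysis): H0 is p_TA = p_DTJIR, and rejecting it establishes a difference.

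The likeliest outcome of the stated test at the planning rates is a nonsignificant P value, which says nothing about whether a 5-point excess has been excluded. The trial could then fail to report a noninferiority result that its data support, or be tempted to treat the absence of significance as support. In either case the primary question would not be judged at the error rate for which the trial was sized.

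**Working it through.** **Inputs (all from Power and Sample Size).** p_TA = 0.05, p_DTJIR = 0.10, margin 0.05, one-sided alpha .025 (z = 1.960), power 0.80 (z = 0.842), 1:1 allocation, dropout 10%.

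**Step 1. Reproduce the sample size** (unpooled variance):

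n = (1.960 + 0.842)² × (0.05×0.95 + 0.10×0.90) / (0.10 − 0.05 + 0.05)²
= 7.849 × 0.1375 / 0.01 = 107.9, so 108 evaluable per arm.

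108 / (1 − 0.10) = 120 per arm. The stated figure reproduces exactly, so the sample size is a margin-based calculation and is not in dispute.

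**Step 2. Compare the two rules by exact binomial enumeration, 108 per arm.** Every pair of event counts is weighted by its binomial probability. The rules are: (a) Pearson chi-square without continuity correction, two-sided .05; (b) upper limit of the two-sided 95% interval for TA minus DTJIR below 0.05, by the Miettinen-Nurminen score method and by the unpooled Wald method.

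| True rates, TA v DTJIR | Chi-square significant | Chi-square nonsignificant | Noninferior (score) | Noninferior (Wald) |
|---|---|---|---|---|
| 5% v 10% (planning) | 29.3% | 70.7% | 77.8% | 81.5% |
| 15% v 10% (worse by the margin) | 20.3% | 79.7% | 2.5% | 2.8% |

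**Step 3. How often the two rules part at the planning rates.** Every table with a significant chi-square in favour of TA also meets the noninferiority rule; the probability of such a table is 29.2%. So noninferiority is met with a nonsignificant chi-square in 77.8% − 29.2%, about 49% of trials, by the score interval, and in 81.5% − 29.2%, about 52%, by Wald.

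**Step 4. Two illustrative results (Wald limits).**

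- 5/108 v 11/108: difference −0.0556, standard error 0.0354, upper limit −0.0556 + 1.96×0.0354 = 0.014. Chi-square P = .12. Noninferiority is shown.
- 14/108 v 11/108: difference 0.0278, standard error 0.0435, upper limit 0.0278 + 1.96×0.0435 = 0.113. Chi-square P = .52. Noninferiority is not shown.

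Under the stated analysis both would be reported only as showing no significant difference, although they answer the primary question in opposite ways.

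**Step 5. Sidedness and alpha.** A one-sided test at .025 against the margin is the same decision as comparing the upper limit of a two-sided 95% interval with the margin. So "With a significance level set at α=.025 (one sided" in the design and two-sided P<.05 in the analysis carry compatible error levels.

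**The case against.** The strongest reply is that the chi-square sentence is a generic default by variable type. It does not name the primary end point, the article is condensed, and a separate analysis plan may hold the noninferiority interval and decision rule. It is true that one can say only of this article that the margin goes unused. But the section is not silent: it names a test for categorical variables, makes its P-value rule universal, and exempts nothing. An analysis plan that used a margin-based test would depart from that text. This is therefore a stated rule that does not fit the design, which differs from detail left out.

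Four stronger readings are tempting and are not supported.

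- A reader might infer that the sections also conflict on alpha and sidedness. They do not, as Step 5 shows.
- A reader might infer that chi-square can never inform the primary question. A significant result favouring TA excludes zero and hence excludes +0.05. The gap concerns every other result.
- A reader might infer that the protocol will declare noninferiority whenever P exceeds .05. It states no such rule. The Discussion's hope of showing TA to be as effective as the comparator is not tied to a nonsignificant test, so the 80% figure is conditional on that misreading. Nor does 29% contradict the planned 80% power, since the two figures concern different hypotheses.
- A reader might infer a fault in the analysis sets. Both intention-to-treat and per-protocol analyses are named for efficacy, and which of them carries the claim is commonly left to the analysis plan.

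**Conclusion.** The point stands, limited to the null hypothesis: the design tests against a 0.05 margin, while the only test stated for the binary primary end point tests equality. At the planning rates with 108 evaluable per arm, the stated test would reach significance in about 29% of trials, and in about half (49% score, 52% Wald) it would be nonsignificant although noninferiority was met. If nonsignificance were read as equal effectiveness, a TA worse by the full margin would pass about 80% of the time against an intended 2.5%.

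These figures assume the protocol's own rates and dropout, independent binomial outcomes, and chi-square without continuity correction. The 80% also assumes the misreading described above. The sample size itself is sound for the noninferiority question under its own assumptions. Because the primary conclusion depends on the test, the text should be corrected before the final analysis.

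**What to change.** In Statistical Analysis, add a primary-analysis statement: the risk difference in 1-year reflux esophagitis (TA minus DTJIR) will be reported with a two-sided 95% confidence interval by a named, prespecified method, and noninferiority will be claimed only if the upper limit is below +0.05, which corresponds to one-sided alpha .025. Limit the chi-square test and the two-sided P<.05 rule to the other comparisons.

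The cost is a few lines of wording, with no extra patients or data. Follow-up runs to February 2028, so there is time to make the change. The choice of interval carries a small trade-off at 108 per arm: a score interval such as Miettinen-Nurminen holds the error at the margin to 2.5% but gives about 78% power, while the Wald interval gives about 81% with 2.8% error. Either cures the mismatch; the method should be named in advance and the trade-off acknowledged.

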### Randomization

Patients can only be randomized into different groups once they have signed the informed consent form, completed baseline assessments, and been confirmed as fully meeting the inclusion criteria. Eligible patients will be randomly assigned to 1 of the following 2 groups at a 1:1 ratio: the tunnel anastomosis group or the double-tract jejunal interposition reconstruction group. The randomization process will use a stratified block randomization method, with disease stage (categorized as early stage or advanced stage) serving as the stratification factor. Patient group assignment will be determined based on random numbers generated by the R software program (version 4.0.2; R Foundation for Statistical Computing).

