This study also has certain inherent limitations. It is not possible to blind patients, surgeons, radiologists, or clinical assessors in this trial. Both the physicians and patients have a clear understanding of the surgical procedure that will be performed. To minimize the bias introduced by the inability to implement blinding, the follow-up and data analysis will be conducted by different people. Meanwhile, as a prospective study, it may have the capacity to mitigate the impact of such bias on the results. The primary end point of this study is the 1-year incidence rate of reflux esophagitis. However, this fails to reflect the long-term antireflux effect. In the future, we will conduct longer-term follow-up to investigate the long-term efficacy of tunnel anastomosis. To increase the dissemination of our research, we will also present our study and its results at a wide range of academic conferences.

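### The surgical-approach subgroup appears to rest on the approach recorded after the operation, which unblinded allocation may influence; this secondary comparison may be biased

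*Protocol article*

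**What the plan says.** All references are to the protocol article.

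- **Statistical Analysis** names disease stage and surgical approach as the two factors for subgroup analysis beyond the overall comparison. It then gives a longer list that begins "Subgroup analyses will be conducted by disease stage (early vs advanced" and continues with "surgical approach (open, laparoscopic, or robot-assisted); age; macroscopic types; and tumor, node, metastasis stage". It treats every P value as two-sided, with .05 as the threshold, and does not label the subgroups exploratory.
- **Data Collection** opens with "Basic patient information and clinical data will be collected before discharge". The items that follow include "surgical approach; duration of surgery; intraoperative blood loss; pathological tumor, node, metastasis staging". Approach thus sits among facts known only once the operation is done. No planned approach is listed.
- **Randomization** states "Patients can only be randomized into different groups once they have signed the informed consent form, completed baseline assessments" and have been confirmed to meet the inclusion criteria. The scheme is a stratified block design "with disease stage (categorized as early stage or advanced stage) serving as the stratification factor". Approach is not a stratum.
- **Surgical Procedure, Overview** allows all three approaches in both arms and does not say when the choice is made.
- **Discussion** (limitations) says that surgeons cannot be blinded and adds "Both the physicians and patients have a clear understanding of the surgical procedure that will be performed".

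**The concern.** A subgroup comparison keeps the protection of randomization only if membership is fixed before allocation or cannot be affected by it. Approach as performed does not clearly meet either condition. A surgeon who knows the assigned reconstruction may choose a different approach because of it, or may convert to open surgery more readily in one arm. The two reconstructions make different technical demands. The tunnel technique involves submucosal dissection and several rows of suturing, while the control technique specifies a linear stapler for the gastrojejunal anastomosis.

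If harder cases leave the laparoscopic group more often in one arm, the remaining laparoscopic patients in that arm are a more favorable selection and the open patients a less favorable one. The two subgroups then err in opposite directions. That can look like a treatment effect that depends on approach when there is none. A reader might conclude that the tunnel technique suits one approach and not another.

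**Working it through.** **1. The plan's own figure.** Inputs from Power and Sample Size: 10% reflux esophagitis with double-tract reconstruction (DTJIR), 5% with tunnel anastomosis (TA), margin 5 points, one-sided alpha 0.025, power 0.80, dropout 10%.

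n per arm = (1.960 + 0.842)² × (0.10×0.90 + 0.05×0.95) / (0.05 + 0.05)² = 7.849 × 0.1375 / 0.01 = 107.9, so 108 evaluable. With dropout, 108 / 0.9 = 120 per arm, as stated. Nothing in this point alters that figure.

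**2. Is approach fixed before allocation?** Randomization is tied to consent, baseline assessments and the inclusion criteria. Approach is not among the stratification factors and appears only in the operative data. The Discussion says that patients understand which procedure they will have, which most naturally means that allocation is known before anesthesia. The article does not say whether approach is chosen before or after that moment. If it is chosen earlier, conversions would still come after allocation.

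**3. Illustration A: conversions only, no true effect.** All inputs are assumptions. A share d = 0.25 of cases is technically difficult, with 20% risk; the others have 5%. All operations start laparoscopically, and a proportion c of difficult cases is converted.

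Laparoscopic-subgroup risk = [d(1−c)×0.20 + (1−d)×0.05] / [d(1−c) + (1−d)]

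- DTJIR, c = 0.10: 0.0825 / 0.975 = 8.46%
- TA, c = 0.30: 0.0725 / 0.925 = 7.84%, spurious TA advantage 0.6 points
- TA, c = 0.40: 0.0675 / 0.900 = 7.50%, advantage 1.0 points
- TA, c = 0.50: 0.0625 / 0.875 = 7.14%, advantage 1.3 points

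**4. Illustration B: choice of approach, no true effect.** All inputs are again assumptions. Two equally common patient types average 10% risk. DTJIR uses minimally invasive surgery in 80% of both types. TA uses it in 80% of low-risk patients but only 40% to 70% of high-risk patients. DTJIR risk is then 10% in both subgroups.

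With risks of 5% and 15%, and TA at 40% in high-risk patients:

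- Minimally invasive: (0.8×0.05 + 0.4×0.15) / 1.2 = 8.3%, a difference of −1.7 points
- Open: (0.2×0.05 + 0.6×0.15) / 0.8 = 12.5%, a difference of +2.5 points

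| Risks | TA minimally invasive use, high-risk | TA−DTJIR, minimally invasive | TA−DTJIR, open |
|---|---|---|---|
| 5%, 15% | 70% | −0.3 | +1.0 |
| 5%, 15% | 40% | −1.7 | +2.5 |
| 2%, 18% | 70% | −0.5 | +1.6 |
| 2%, 18% | 40% | −2.7 | +4.0 |

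If approach does not depend on arm, every difference is 0.

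**5. Scale against sampling error.** Even if all 108 evaluable patients per arm fell in one subgroup at about 8% risk, the standard error of the difference would be √(2×0.08×0.92/108) = 3.7 points, a 95% interval of about ±7 points. The largest bias in Illustration A is about a third of that standard error (1.3 / 3.7).

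**The case against.** **The classification of conversions belongs in the analysis plan.** The article does not say that the subgroup uses the approach after conversion, and the full protocol and analysis plan are not shown. This stands in part: the as-performed reading is inferred from the data list. But an analysis plan can use the planned approach only if someone recorded it, and the article lists approach only among operative data.

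**The timing is not stated.** This stands. Some exclusion criteria rest on intraoperative findings, so even the moment of randomization is not pinned down. If approach is settled before allocation, only conversions remain as a route.

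**The mechanism is speculative and the effect small.** The article never mentions conversion, TA also uses a stapler for transection, and every input above is assumed. The 1.3-point figure needs TA to convert difficult cases five times as often as DTJIR. This also stands. The illustrations show direction and plausible scale, and they are not estimates. The 5-point margin was set for the overall comparison, so it is only a yardstick here.

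**A stronger reading to avoid.** A reader might infer that the tumor, node, metastasis (TNM) subgroup has the same defect, because Data Collection lists only "pathological tumor, node, metastasis staging". The documents do not support that. Resection is common to both arms and the extent of dissection follows clinical stage, so the assigned reconstruction has no direct route to pathological stage. A factor measured after randomization but not affected by it does not bias the comparison. The article also does not say which TNM stage defines the subgroup, and the early/advanced stratum is already a separate subgroup.

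**Conclusion.** The point holds for surgical approach only. Followed as written, the plan appears to condition on an operative variable that unblinded surgeons choose or change, so allocation may shape the approach subgroups. The bias is possible, not shown. It depends on approach or conversion differing by arm in a way related to reflux risk. Under the assumed patterns it runs from 0.3 to 2.7 points in one direction and 1.0 to 4.0 points in the other, and it vanishes if approach is independent of arm.

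The point should not be carried over to the primary result. All randomized patients enter the overall intention-to-treat comparison whatever the approach, so the noninferiority conclusion and the 240-patient sample size are untouched. This is a limited flaw in a secondary analysis, and worth correcting because the remedy is cheap.

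**What to change.** 1. Add a field for the planned approach, completed before randomization.
2. State in Statistical Analysis that the approach subgroup is defined by the planned approach and that converted patients stay in their planned group.
3. Report the actual approach and conversions by arm descriptively.
4. For patients already enrolled, take the planned approach from preoperative notes where these exist. Where they do not, present the as-performed subgroup as a non-randomized, exploratory comparison.

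The cost is one field and one or two sentences. Enrollment began in March 2022, so data for earlier patients will be incomplete or retrospective across six centers, and staff who know the allocation may be the ones to extract them. Recruitment is scheduled to run to February 2027, so prospective capture may still be possible for later patients. If the full protocol already records the planned approach, only the sentences on its use are needed.
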